### Secondary outcomes

Urinary pesticide metabolites and dietary diversity at 24 months will be assessed as secondary outcomes. In addition, the following secondary outcomes will be measured at 12 and 24 months post-randomisation.

Fasting plasma glucose. A trained phlebotomist will collect an overnight fasting blood sample. Once collected, the sample will be placed in an insulated box on ice packs and transported to the laboratory for processing and same-day analysis of glucose by the hexokinase method [88].Estimated glomerular filtration rate will be calculated using the Modification of Diet in Renal Disease Study equation [89]. Serum creatinine will be measured using the Jaffe’s method, calibrated using Isotope Dilution Mass Spectroscopy (IDMS) traceable-creatinine. Blood pressure will be measured in order to differentiate between chronic kidney disease (CKD) and CKD of unknown aetiology (CKDu). Systolic and diastolic blood pressure will be measured in triplicate with at least 2 minutes resting between repeat measurements using an automatic blood pressure monitor (Omron JPN1) after leaving the person rested and seated for at least 5 minutes before taking the first measurement. The average of the second and third measurements will be used in the analysis.Urine protein-to-creatinine ratio will be measured using the first sample of two spot urine samples collected from the adult participants. Urine protein will be measured using the pyrogallol red-molybdate method. Urine creatinine will be measured using the Jaffe’s method.Adult nutritional status. Weight and height of adults will be measured based on the National Health and Nutrition Examination Survey protocol [90] using electronic scales (Seca 874) and portable stadiometers (Seca 213). Adult BMI will be calculated as weight (kg) divided by height-squared (m^2^) and categorised as underweight (BMI <18.5 kg/m^2^), normal weight (BMI 18.5 to <25 kg/m^2^), and obesity including overweight (BMI ≥25 kg/m^2^) [91]. Haemoglobin will be measured in venous blood samples using photometry. Anaemia will be defined as haemoglobin <12 g/dL in non-pregnant women, haemoglobin <11 g/dL in pregnant women, and haemoglobin <13 g/dL in men, according to the WHO guidelines [92].Self-reported musculoskeletal pain and clinical symptoms. Musculoskeletal pain and clinical symptoms in the past 3 months will also be queried. Symptoms will include itchy skin, rash on skin, dry/cracking skin, blisters on the skin, fatigue or weakness, headache, dizziness, eye irritation or watering, pain in the eye, redness in the eye, blurry vision, chest pain / tightness, difficulty breathing, and digestive problems (e.g., nausea, vomiting, stomach cramp, diarrhoea). The list of symptoms was adapted from a survey on pesticide use in Thailand [93].Depressive symptoms. Depressive symptoms will be assessed using the Patient Health Questionnaire (PHQ, 9 items) [94], which has been used previously in this context [95, 96]. The questionnaire asks participants how often (not at all, several days, more than half of the days, or nearly every day) over the last 2 weeks they have been bothered by problems such as having little interest or pleasure in doing things; having trouble concentrating on things; and thoughts that they would be better off dead or of hurting themselves in some way. Given the sensitive nature of these questions, the survey will be completed in a private area and data collectors will confirm with the participant that they feel comfortable before beginning the survey.Women’s Empowerment. Women’s empowerment will be measured using the abbreviated Women’s Empowerment in Agriculture Index (A-WEAI) [97] and the abbreviated Women’s Empowerment in Nutrition Index (A-WENI) [98]. The A-WEAI assesses women’s empowerment and inclusion in agriculture. It covers five domains: production, resources, income, leadership, and time. The A-WENI assesses women’s nutritional empowerment or women’s capacity to be healthy and well fed. It covers seven domains: food knowledge, food resources, food agency, health knowledge, health resources, health agency, and institutions. For both A-WEAI and A-WENI, domain-specific scores and total empowerment scores will be calculated.Child growth (length/height-for-age z-score). Child length (≤2 years) and height (>2 years) will be measured using a portable length board (Seca 417) or stadiometer (Seca 213). Child stunting will be defined as length/height-for-age z-score < -2 SD below the median z-score based on WHO Child Growth Standards [99].Child development. At baseline, the Caregiver-Reported Early Development Instruments (CREDI), will be used to assess child development in children <38 months of age [100]. At 12 and 24 months post-randomisation, we will use the Parents’ Evaluation of Developmental Status:Developmental Milestones (PEDS:DM) to assess child development [101]. Both CREDI and PEDS:DM assesses motor, cognitive, language, and socio-emotional development based on caregiver report. We will assess raw scores, sample-standardised scores, and norm-referenced standardised scores.Household crop yield will be collected via self-report using questions adapted from the Indian National Sample Survey Office’s (NSSO) Situation Assessment Survey of Agricultural Households [102].Household income, expenditures, and debt will be collected via self-report using questions adapted from the NSSO Situation Assessment Survey of Agricultural Households [102].

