## Methods

### Aims

The primary aim of this study is to determine if a community-based agroecology programme implemented by the state government of Andhra Pradesh in India results in lower urinary pesticides and higher dietary diversity among adults and children in agricultural households, as compared to standard agricultural practices (primary outcomes).

Secondary aims include to determine whether this programme improves crop yields, household income, adult anthropometry, anaemia, glycaemia, kidney function, musculoskeletal pain, clinical symptoms, depressive symptoms, and women’s empowerment, and child growth and development in the same adults and children (secondary outcomes).

In an a priori secondary analysis, data collected on compliance with APCNF practices will be used to estimate the per-protocol effect of APCNF on the outcomes.

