### Statistical analysis plan

The main analyses will be intent-to-treat, i.e., participants will be analysed as assigned, regardless of their fidelity to APCNF practices. Herein the analyses for primary outcomes are described. Analyses for secondary outcomes will be analogous. Separate models will be run for each of the primary outcomes. All primary outcomes are continuous. General estimating equation (GEE) models with robust standard errors will be used to account for within-participant correlations [111]. Models will account for clustering within villages. The models will take the form of:

$$Y_{i,t}=\beta_{0}+\beta_{1}Group+\beta_{2}Time+\beta_{3}Group*Time+\beta_{4}District+\varepsilon_{i,t}$$
(1)

where group is APCNF or control, time is baseline or 12 months, and district is Kurnool or Visakhapatnam (to account for randomisation stratification). β_3_ represents the difference in the change from baseline to 12 months in the APCNF group and the change from baseline to 12 months in the control group (e.g., difference in difference).

We will evaluate whether missing data are differential between groups using t-tests. We will assume missing data to be missing at random and conduct a complete-case analysis. Inverse probability weighting will be used to account for loss to follow-up. We will run adjusted models to address potential baseline imbalance across clusters and improve precision. Covariates will be selected based on p-values for differences across groups.

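### Child development is measured with CREDI at baseline and PEDS:DM at follow-up, but the analysis rule for secondary outcomes, read as written, makes the effect a change between the two instruments

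*Protocol article*

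**What the plan says.** Under Secondary outcomes, the Protocol article sets the baseline instrument, "At baseline, the Caregiver-Reported Early Development Instruments (CREDI), will be used to assess child development in children <38 months of age", and a different one for follow-up: "At 12 and 24 months post-randomisation, we will use the Parents’ Evaluation of Developmental Status:Developmental Milestones (PEDS:DM) to assess child development". The stated link between them is content and mode of report: "Both CREDI and PEDS:DM assesses motor, cognitive, language, and socio-emotional development based on caregiver report". Three forms of score are planned: "We will assess raw scores, sample-standardised scores, and norm-referenced standardised scores". No linking or equating of the two instruments is described. Table 1 lists them together as the metric for early child development.

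The Statistical analysis plan section gives one model, equation (1), with group, time, their product and district. The definition of its terms, "where group is APCNF or control, time is baseline or 12 months", places the baseline measurement in the outcome vector. The effect is β3, which "represents the difference in the change from baseline to 12 months in the APCNF group" relative to the same change in controls. For everything else the section says: "Analyses for secondary outcomes will be analogous". Child development is among these outcomes; the Aims list "women’s empowerment, and child growth and development in the same adults and children (secondary outcomes". No exception is made for it.

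**The concern.** A difference-in-change model needs the same quantity measured at both times. Here the baseline value would be a CREDI score and the follow-up value a PEDS:DM score. Subtracting one from the other does not give a child's change in development. On raw scores the two values are in different units, and the time coefficient β2 partly reflects the gap between the scales. On standardised scores the units are comparable, but the contrast is still between two instruments.

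The model also fixes the weight on baseline CREDI at 1 instead of estimating it. A chance group difference in CREDI therefore passes in full into the estimate, and precision may be lost. Early child development is one of the areas in which the Discussion expects the study to give first evidence, so its effect estimate should have a clear meaning.

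**Working it through.** **Inputs from the article.** CREDI at baseline; PEDS:DM at 12 and 24 months; raw, sample-standardised and norm-referenced scores (Secondary outcomes). Baseline inside the outcome, β3 as the effect, secondary analyses analogous (Statistical analysis plan). The article gives no SD, effect size or power for child development, and Table 5 covers only primary outcomes, so there is no figure to reproduce.

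**Assumed inputs.** k = SD of CREDI divided by SD of PEDS:DM; r = correlation between the two. Neither is in the document, so ranges are shown. The same r and intra-cluster correlation are taken to apply to both instruments, so clustering cancels from the ratios.

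**Step 1: write out the effect.** Apart from weighting and the district term, equation (1) gives

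β3 = (PEDS:DM mean, APCNF − PEDS:DM mean, control) − (CREDI mean, APCNF − CREDI mean, control).

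**Step 2: expectation.** Under randomisation the second bracket has expectation zero, so β3 is centred on the PEDS:DM group difference. A simulation with 80 clusters of 25 children, intra-cluster correlation 0.02, assumed r = 0.4, no true effect and no imbalance gave mean β3 close to 0 (−0.002 and −0.010 raw points under two assumed pairs of SDs).

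**Step 3: chance imbalance.** The CREDI difference is subtracted one-for-one. In the same simulation, CREDI was shifted by 0.1 SD in one group and PEDS:DM left unchanged:

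- Raw scores, assumed SDs CREDI 12 and PEDS:DM 5: expected −0.1 × 12 = −1.2; simulated −1.22 points.
- Raw scores, assumed SDs CREDI 5 and PEDS:DM 12: expected −0.1 × 5 = −0.5; simulated −0.52 points.
- Sample-standardised scores: simulated −0.10 SD.

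A real chance imbalance of d CREDI SDs would on average come with a PEDS:DM difference of r × d SDs. The net shift is then (r − k) × d in PEDS:DM SD units. For d = 0.1, k = 1 and r = 0.3 it is (0.3 − 1) × 0.1 = −0.07 SD.

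**Step 4: precision.** Set the PEDS:DM SD to 1.

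- Change model: variance proportional to 1 + k² − 2rk.
- PEDS:DM adjusted for baseline CREDI: variance proportional to 1 − r².
- Difference: (1 + k² − 2rk) − (1 − r²) = (k − r)², which is never negative and is zero only if k = r.

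At r = 0.3:

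| k | Change model | Baseline-adjusted | Variance ratio |
|---|---|---|---|
| 0.3 | 1 + 0.09 − 0.18 = 0.91 | 0.91 | 1.00 |
| 0.5 | 1 + 0.25 − 0.30 = 0.95 | 0.91 | 1.04 |
| 1 | 1 + 1 − 0.60 = 1.40 | 0.91 | 1.54 |
| 2 | 1 + 4 − 1.20 = 3.80 | 0.91 | 4.18 |

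If each visit is standardised separately in the sample, k is about 1 and the ratio simplifies to 2/(1 + r): 1.54 at r = 0.3 and 1.33 at r = 0.5. In that case the change model is also less precise than ignoring baseline altogether whenever 2 − 2r > 1, that is, r < 0.5.

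**The case against.** The strongest reply is that no sentence applies equation (1) to child development by name. The section says that it describes the primary outcomes, and analogous is not identical. Some adaptation is unavoidable: the time factor in equation (1) stops at 12 months, while secondary outcomes are also measured at 24, and several of them are categorical. A full analysis plan, not shown here, may treat child development separately. This stands as a limit on how firmly the problem can be asserted. It does not remove it, because the article states a rule, extends it to all secondary outcomes, and the rule fails for this one.

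A second reply is that standardised scores are planned. They largely remove the unit mismatch. Raw scores are planned too, however, and standardising does not turn two instruments into one or free the slope of 1.

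A third is that the adjusted models would absorb baseline imbalance. They would not do so for CREDI: it already sits inside the outcome, so its weight in β3 stays at 1.

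On size, a reader might infer that variance must be inflated several-fold. The documents do not support that. Such figures need a raw-score SD ratio well above 1, which is an assumption; at k near r almost nothing is lost. The 1.54 at k = 1 is the ordinary cost of change scores against baseline adjustment and would arise at the same r with a single instrument.

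**Conclusion.** The concern holds as a mismatch between the measurement plan and the stated analysis rule for one secondary outcome. Followed as written, β3 is a contrast between two instruments with the slope forced to 1. It cannot be read as a change, most clearly on raw scores, and it passes on chance CREDI imbalance in full. That it is never more precise than baseline adjustment follows from (k − r)² ≥ 0, whatever the values of k and r. How much precision is lost rests on assumed values: at r = 0.3, from nothing at k = 0.3 to a variance ratio of 1.54 at k = 1, and 4.18 at k = 2, which is possible for raw scores only.

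Two stronger readings are tempting and should be resisted. A reader might infer that the estimate is biased; under randomisation it is not, in expectation. A reader might also infer that changing instrument between visits is itself an error; nothing in the article shows that, and the issue is only the model that is carried over. Child development is one item in an unranked list of secondary outcomes and has no power calculation, so the point is worth correcting but does not touch the primary analysis.

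**What to change.** Add a sentence to the Statistical analysis plan section that excepts child development from the general rule. PEDS:DM at 12 and at 24 months would be compared between groups with baseline CREDI as a covariate and district in the model, using robust standard errors clustered by village. CREDI then gets its own estimated slope, and the effect is expressed in PEDS:DM units. Child age and sex can be added to gain precision, but the correction does not depend on them.

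The cost is a wording change. CREDI, PEDS:DM, age and sex are all already planned for collection, and the Study status section places the end of baseline assessment and the start of implementation in February 2023, before any follow-up scores exist.

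If a separate analysis plan already treats child development this way, the article's rule should be reconciled with it.

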
### Additional assessments

Demographic and socio-economic data will be collected at baseline for all participants using questions adapted from the 5^th^ round of the Indian National Family Health Survey (NFHS-5) [5]. Specific variables to be assessed include age, sex, marital status, educational attainment, occupation, caste, cooking fuel, source of drinking water, toilet facility, household construction materials, and asset ownership including livestock. A household wealth index will be calculated from these variables using principal components analysis.

Information on cropping pattern, land cultivated, land irrigated, and land owned, in both Kharif (monsoon season) and Rabi (winter season), will be collected using questions adapted from the Indian Agriculture Census [103] and NSSO Situation Assessment Survey of Agricultural Households [102]. Farmer estimates will be used to estimate crop yields, quantity sold, where it was sold, and the sale value. This survey will also include questions on chemical input use, pesticide storage, and all expenses relating to crop production in the past 12 months (seeds, soil, fertilisers, manure, pesticides, diesel, electricity, human labour, animal labour, irrigation, minor repairs and maintenances, machinery hire, and lease rent for land). Detailed information will be collected from all adult participants on years working in agriculture; how many days per week and hours per day engaged in agricultural work; and which specific agricultural activities are undertaken. For those reporting activities relating to pesticides (e.g., mixing, loading, and/or application), additional information on chemicals used, application rate, method of mixing, method of application, use of personal protective measures and/or equipment, and personal hygiene practices will be collected. This survey will also query domestic use of pesticides for insect control. Questions are adapted from a survey on pesticide use in Thailand [93].

We will measure key practices emphasised by the APCNF programme in order to quantify fidelity. Indicators, as provided by RySS, will include poly cropping, inter cropping, multi-layer cropping, border crops, trap crops, fruit trees, pre-monsoon dry sowing, cattle grazing on pre-monsoon dry sowed crop, 365 days green cover, indigenous seeds, Beejamrutham seed coating, minimal tillage, mulching, manual weeding, mechanical weeding, irrigation, botanical inputs for pest management, pheromone and sticky traps for pest management, use of Jeevamruth, and use of cattle manure.

Self-reported medical history and current medication use will be assessed for all participants. Diseases will include diabetes, hypertension, high blood cholesterol, heart disease/angina/heart attack/stroke, chronic kidney disease, kidney stones, asthma/chronic obstructive pulmonary disease/emphysema, cancer, and cataracts. We will also collect information on pesticide poisoning (both intentional and unintentional). Information will be collected from women on their number of pregnancies and number of live births.

### Collection and storage of biological specimens

Urine and blood samples will be collected at three time points from adults, and urine at three time points for children in up to 12 households per cluster. Sample aliquots will be stored at -80°C in New Delhi, India at the Public Health Foundation of India’s biospecimens repository.

### Power calculations

Power calculations were conducted using PASS 2019, v19.0.6 (NCSS, Kaysville, Utah, USA), accounting for the cluster-randomised design. Whilst hypotheses for the two primary outcomes (urinary pesticides and dietary diversity) were independent, in order to be conservative, a Bonferroni correction was applied (0.05/2, which is the number of primary outcomes) resulting in a two-sided alpha level of 0.025. It is expected that approximately 20% of the baseline sample will be loss-to-follow-up at 12 months. Two previous surveys in Andhra Pradesh by study team members had much lower loss to follow-up rates [2% from 2019 to 2020 in the SHEFS (Sustainable and Healthy Food Systems) nutrition survey (unpublished) and 10% for the mWellcare trial [104] but a higher rate was anticipated for the BLOOM study due to COVID-19.

Power for the primary outcomes is given in Table 5, which summarises the minimal detectable difference in mean levels associated with 80% power, a type I error rate alpha of 0.025, an intra-cluster correlation of 0.02, and 20% loss to follow-up. For ∑DAPs power calculations are shown for 150 per arm (a 15% subsample). Results in Table 5 confirm that the study is adequately power to detect a smaller difference than has been previously reported in the literature for these outcomes.

**Table 5 pone.0281677.t005:** Minimum detectable mean difference, with 80% power, alpha = 0.025, and intra-cluster correlation of 0.02.

	Standard Deviation for Mean Change in Outcome	Sample Size per Group	Minimum Detectable Mean Difference	Previous Study Estimate (95% Confidence Interval)
Change in mean ∑DAPs, adult men	111 μmol/l*	150	39.6 μmol/l (~55% of estimated baseline levels*)	-88% (not reported)^†^
Change in mean ∑DAPs, adult women	111 μmol/l*	150	39.6 μmol/l (~55% of estimated baseline levels*)	-88% (not reported)^†^
Change in mean ∑DAPs, children	17.3 nmol/l^‡^	150	6.17 nmol/l (~9.7% of estimated baseline levels^‡^)	-42.7% (-76.3–38.7)^‡^ -39.9% (-58.6, -12.6)^§^
Change in mean dietary diversity score, adult women	1.57^¶^	1000	0.29	0.36 (0.03–0.69)^¶^
Change in mean dietary diversity score, children	1.40^#^	1000	0.26	0.39 (0.13–0.64)^#^

* From an observational study of adult agricultural labourers in North Carolina [105].

^†^ From an observational cross-sectional study comparing organic and conventional vegetable farmers in Thailand [106]. Difference is for urinary levels of 3,5,6-trichloro-2-pyridinol, a metabolite of chlorpyrifos, a specific organophosphate.

^‡^ Percent reduction in ∑DAPs reported for children under 4 years old participating in a home-based educational intervention to reduce take-home pesticides by agricultural labourers in California, USA [107]. Change is from baseline to 3 months.

^§^ Percent reduction in ∑DAPs reported for children 3–6 years old living in urban or agricultural communities in California, USA, who were fed organic food for 4 days [108]. Change is between the control period (9 days) and intervention period (7 days).

^¶^ From a cluster-randomised controlled trial of a nutrition-sensitive agroecology intervention in Tanzania for which a secondary outcome was minimum dietary diversity among women [30]. The estimates used in these power calculations are from the 12-month follow-up visit. Dietary diversity was assessed using the FAO’s minimum dietary diversity score for women, the same as BLOOM. The standard deviation for mean change in outcome is estimated from the control group.

^#^ From a cluster-randomised controlled trial of a nutrition-sensitive agroecology intervention in Tanzania for which the primary outcome was dietary diversity among children aged <1 year at baseline [30]. The estimates used in these power calculations are from the 12-month follow-up visit. Dietary diversity was assessed using the older version of the WHO’s minimum dietary diversity score that did not include breastmilk and so was out of a total of seven food groups instead of eight. The standard deviation for mean change in outcome is estimated from the control group.

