## Abstract

The BLOOM study (co-Benefits of Largescale Organic farming On huMan health) aims to determine if a government-implemented agroecology programme reduces pesticide exposure and improves dietary diversity in agricultural households. To achieve this aim, a community-based, cluster-randomised controlled evaluation of the Andhra Pradesh Community-managed Natural Farming (APCNF) programme will be conducted in 80 clusters (40 intervention and 40 control) across four districts of Andhra Pradesh state in south India. Approximately 34 households per cluster will be randomly selected for screening and enrolment into the evaluation at baseline. The two primary outcomes, measured 12 months post-baseline assessment, are urinary pesticide metabolites in a 15% random subsample of participants and dietary diversity in all participants. Both primary outcomes will be measured in (1) adult men ≥18 years old, (2) adult women ≥18 years old, and (3) children <38 months old at enrolment. Secondary outcomes measured in the same households include crop yields, household income, adult anthropometry, anaemia, glycaemia, kidney function, musculoskeletal pain, clinical symptoms, depressive symptoms, women’s empowerment, and child growth and development. Analysis will be on an intention-to-treat basis with an a priori secondary analysis to estimate the per-protocol effect of APCNF on the outcomes. The BLOOM study will provide robust evidence of the impact of a large-scale, transformational government-implemented agroecology programme on pesticide exposure and dietary diversity in agricultural households. It will also provide the first evidence of the nutritional, developmental, and health co-benefits of adopting agroecology, inclusive of malnourishment as well as common chronic diseases.

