### Primary outcomes

Urinary pesticide metabolites at 12 months in a 15% random subsample of adult men enroled in the study. Six common dialkylphosphate (DAP) metabolites of organophosphorus insecticides will be measured in an equal-volume composite urine sample consisting of two spot urine samples collected within a one-week period. Compositing samples reduces intra-person variability. The six DAPs will include: dimethylphosphate (DMP), dimethylthiophosphate (DMTP), dimethyldithiophosphate (DMDTP), diethylphosphate (DEP), diethylthiophosphate (DETP), and diethyldithiophosphate (DEDTP). Together, these six DAPs cover approximately 77% of organophosphorus insecticides produced in India (Table 4) [11]. Total DAP molar weight (∑DAPs) will be calculated by multiplying the concentration of each of the six DAPs by the molar weights of the respective DAP and summing them. Specific gravity-adjusted ∑DAPs will be analysed as the primary outcome. Specific gravity will be measured in the composite urine sample using a handheld refractometer (Atago PAL-10S). Urine aliquots will be shipped on dry ice to the laboratory for analysis in random sequence using gas chromatography-mass spectrometry (GC-MS) [84]. Laboratory technicians will be blinded to the randomisation status of samples.Urinary pesticide metabolites at 12 months in a 15% random subsample of adult women enroled in the study. The same method, as described above for adult men, will be used to assess specific gravity-adjusted ∑DAPs in adult women.Urinary pesticide metabolites at 12 months in a 15% random subsample of children enroled in the study. The same method, as described above for adult men, will be used to assess specific gravity-adjusted ∑DAPs in children.Dietary diversity score at 12 months in all adult men enroled in the study. Dietary intake of adults will be assessed using a single 24-hour dietary recall. Participants will be taken through the previous day from morning to evening and asked to recall all foods and beverages consumed and the portion size. A standard set of locally appropriate plates, bowls, and cups and show cards will be used to aid portion size estimation. Dietary diversity will be calculated using the FAO’s Minimum Dietary Diversity for Women (MDD-W) [85]. Ten food groups are included: (1) starchy staples (rice, wheat, and potatoes), (2) legumes and pulses, (3) nuts and seeds, (4) dark green leafy vegetables, (5) vitamin-A rich fruits and vegetables, (6) other vegetables, (7) other fruits, (8) dairy products, (9) eggs, and (10) flesh foods (meat, poultry, and fish). For analysis, men who consume a food group on the previous day will be assigned a value of 1 and those who do not will be assigned a value of 0 and the values across these ten food groups will be summed in a dietary diversity score. Thus, the dietary diversity score can range from 0 to 10 with 10 representing maximum dietary diversity.Dietary diversity score at 12 months in all adult women enroled in the study. The same method, as described above for adult men, will be used to assess dietary diversity in adult women.Dietary diversity score at 12 months in all children enrolled in the study. Dietary intake of children will be assessed using the standard WHO Infant and Young Child Feeding practices survey [86], adapted to the local context and administered to the primary caregiver of the child. Dietary diversity will be calculated using the WHO’s dietary diversity score (DDS). Whilst this was originally developed for children 6–23 months old, DDS can serve as an adequate proxy for micronutrient intake in children 24–59 months as well [87]. Eight food groups are included: (1) breast milk, (2) grains, roots, tubers, and plantains, (3) pulses, nuts, and seeds, (4) vitamin-A rich fruits and vegetables, (5) other fruits and vegetables, (6) dairy products, (7) eggs, and (8) flesh foods (meat, poultry, and fish). For analysis, children who consume a food group on the previous day will be assigned a value of 1 and those who do not will be assigned a value of 0 and the values across these eight food groups will be summed. Thus, DDS can range from 0 to 8 with 8 representing maximum dietary diversity.

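### Alpha is divided by two as the number of primary outcomes, but six primary outcomes are listed and modelled separately, so 0.025 per test does not secure 5% overall

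*Protocol article*

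**What the plan says.** The Power calculations section speaks of two primary outcomes and states that "a Bonferroni correction was applied (0.05/2, which is the number of primary outcomes) resulting in a two-sided alpha level of 0.025". It presents this step as more cautious than was strictly required, and the reason it gives is: "Whilst hypotheses for the two primary outcomes (urinary pesticides and dietary diversity) were independent, in order to be conservative". Table 5 is then built at 80% power, alpha 0.025 and an intra-cluster correlation (ICC) of 0.02.

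The Abstract states: "Both primary outcomes will be measured in (1) adult men ≥18 years old, (2) adult women ≥18 years old, and (3) children" (the age limit for children follows). The Primary outcomes section turns this into six separate entries. Three are for urinary metabolites, beginning with "Urinary pesticide metabolites at 12 months in a 15% random subsample of adult men enroled in the study" and "Urinary pesticide metabolites at 12 months in a 15% random subsample of adult women enroled in the study" and then children. Three are for diet, beginning with "Dietary diversity score at 12 months in all adult men enroled in the study" and then women and children. Children's diet is scored on a different scale from adults' (0 to 8 against 0 to 10).

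The Statistical analysis plan section says: "Separate models will be run for each of the primary outcomes". It gives no test level and no rule for combining the populations. Table 5 has separate rows for men, women and children for ∑DAPs and for women and children for diet, all at 0.025. Men's dietary diversity has no row.

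**The concern.** A Bonferroni divisor must equal the number of tests over which error is to be controlled. Here the divisor is two and the planned primary tests number six. Nothing in the article pools the three populations, ranks them, or requires all three to succeed before a domain is claimed. The Aims section mentions adults and children together but attaches no decision rule.

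The correction is presented as conservative. If each population is in fact tested at 0.025 and read on its own, it is not. A chance result for one measure in one population could then be presented as a primary effect of a state-wide programme whose findings, according to the Discussion, are meant to move quickly into policy.

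**Working it through.** **Inputs.** From Power calculations and Table 5: divisor 2; two-sided alpha 0.025; 80% power; ICC 0.02; 20% loss; SDs 111 (adult ∑DAPs), 17.3 (child ∑DAPs), 1.57 (women's diet), 1.40 (children's diet); 150 per arm for ∑DAPs and 1000 per arm for diet. From Study design: 40 clusters per arm. From Primary outcomes: six outcomes. The correlation between test statistics is not given, so it is varied as an assumption. Man, woman and child come from the same household, so some positive correlation is likely.

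**1. The plan's own alpha.** 0.05/2 = 0.025, as stated. For two tests, 1 − 0.975² = 4.9%, with bound 2 × 0.025 = 5%. The correction works if there are two tests.

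**2. Table 5 does use 0.025 for each population.** MDD = SD × √(2·DE/n) × (critical value + power quantile), with DE = 1 + (m − 1) × 0.02 and m = n/40.
- Diet: n = 800 after 20% loss, m = 20, DE = 1.38, t with 78 df. Women 0.289 (stated 0.29); children 0.258 (stated 0.26).
- ∑DAPs: n = 150, normal quantiles 2.241 + 0.842. Without a design effect, adults 39.5 (stated 39.6) and children 6.16 (stated 6.17). With DE = 1.055, 40.6 and 6.33.

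All are within 3% of the printed values.

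**3. Six tests at 0.025.** Bound: 6 × 0.025 = 15%. Independent: 1 − 0.975⁶ = 14.1%. Within one domain, three independent tests give 1 − 0.975³ = 7.3% instead of 2.5%.

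**4. Allowing for correlation** (simulation, 2,000,000 draws):

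| Assumed correlation | Domains independent, correlated within | All six equally correlated |
|---|---|---|
| 0.3 | 13.6% | 13.0% |
| 0.5 | 12.7% | 11.2% |
| 0.7 | 11.2% | 9.0% |
| 0.9 | 8.6% | 5.8% |
| 1.0 | 4.9% | 2.5% |

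The middle column follows the protocol's own statement that the two domains are independent. The error reaches 5% or less only near perfect correlation.

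**5. Effect of dividing by six.** 0.05/6 = 0.0083. Six independent tests then give 1 − (1 − 0.0083)⁶ = 4.9%, with bound 5%.

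| Table 5 row | Stated MDD | MDD at 0.0083 | Cited prior effect |
|---|---|---|---|
| Diet, women | 0.29 | 0.33 | 0.36 |
| Diet, children | 0.26 | 0.29 | 0.39 |
| ∑DAPs, adults | 39.6 (~55%) | 45.8 (~64%) | 88% |
| ∑DAPs, children | 6.17 (~9.7%) | 7.1 (~11%) | 39.9% and 42.7% |

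The percentages use the baselines that Table 5 implies: 39.6/0.55 = 72 and 6.17/0.097 = 63.6. Like for like, the increase is 13 to 14% (0.289 to 0.328; 40.6 to 45.8). Against the printed 39.6 it looks nearer 16%, because 45.8 includes the design effect and 39.6 is matched more closely without it.

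By the normal approximation, power at the printed MDDs falls from about 78–82% to 64–70%. Against the cited diet effects it goes from 95% to 90% (women) and from 99% to 98% (children).

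**The case against.** The strongest reply has three parts.

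First, the protocol consistently describes two primary outcomes measured in three populations, and it is arguable that men, women and children are separate questions, each with its own estimate. Control over all six tests is one legitimate choice among several. But the protocol chose to correct and gave the number of primary outcomes as the divisor. Its own list of those outcomes has six entries, so the two sections conflict whichever philosophy is preferred. The remark about independence concerns pesticides versus diet, not three tests of one measure.

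Second, the level 0.025 appears only in the power section, and an analysis plan that is not shown may set a decision rule. That is correct, and silence about such a rule is not the complaint. The stated divisor is. An analysis plan that divides by six would depart from Table 5, and one that keeps 0.025 needs an ordering, pooling or joint-success rule that this text lacks.

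Third, the size is uncertain. A reader might infer that the trial's family-wise error simply is 13 to 15%, or that the plan declares any single positive result a success. The documents support neither. The 15% is only an upper bound, 14.1% requires independence, no correlation is reported, and the any-one-of-six rule is written nowhere. Nor does the mismatch overturn Table 5's conclusion on adequacy, because every restated MDD remains below its cited benchmark.

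**Conclusion.** The point stands as a mismatch in the current text: alpha is divided by two, while six primary outcomes are listed, modelled separately and, for the five with a row in Table 5, powered separately at 0.025. The conditional error in steps 3 and 4 rests on two assumptions: each of the six is judged at 0.025, and any one significant result counts as a primary finding. Under these it lies well above 5% for any plausible correlation and approaches 5% only when the tests are almost duplicates. The consequence is for how results may be claimed, not for sample size. It should be settled before any unblinded analysis.

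**What to change.** Reconcile the Power calculations and Primary outcomes sections, and state one rule before unblinding. Either:

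- control the family-wise error at 5% over all six tests with Holm, or with Bonferroni at 0.05/6; or
- keep 0.025 per domain and prespecify the order of the three populations within each domain, testing the next only if the previous one is significant.

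Under Bonferroni, restate Table 5 at 0.0083, with MDDs of about 0.33 (women's diet), 0.29 (children's diet), 46 (adult ∑DAPs) and 7.1 (child ∑DAPs). Under either option, add the missing row for men's dietary diversity. The protocol gives no SD for men; if the women's 1.57 is assumed, the MDD at 0.0083 would also be about 0.33.

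The cost is a change of wording and a recalculated table. Bonferroni brings the larger MDDs shown above, and Holm costs less. The fixed order leaves 0.025 intact, but a population placed after a non-significant one can no longer support a primary claim. No option needs more clusters or participants to meet the benchmarks that Table 5 cites.
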